### Covariates

The following covariates will be accounted for when analysing the results: sex, age, socioeconomic status, child well-being and parental MSK health.

### Length of follow-up

The duration of the follow-up will be 12 years, which covers three years in preschool and nine years in school.

### Analyses

Multilevel logistic regression will be conducted to determine if there was a difference in aberrant movement problems by intervention group after adjusting for time in intervention, imbalanced covariates from WP1, school and socioeconomic status of the school.

Multilevel Poisson regression will be conducted if the number of MSK diagnoses of persistent problems differs by intervention group after adjusting for time on intervention, imbalanced covariates from WP1, school and socioeconomic status of the school.

The age-specific, sex-specific and age- and sex-specific incidence rate of MSK conditions will be calculated.

Longitudinal latent class analysis and latent class growth analysis will be conducted to describe the MSK developmental patterns. The sequential model comparisons (T classes vs. T + 1 classes) and chi-square goodness-of-fit test will be evaluated using the parametric bootstrapping technique. Lastly, the associations between class membership and the prevalence of related measures will be examined using a confirmatory latent class analysis approach.

Multilevel longitudinal logistic regression analyses will be conducted to determine if poor motor performance is associated with aberrant movement patterns after adjusting for age, sex and other important covariates. The interaction between time and poor motor performance will be examined.

Multilevel longitudinal Poisson regression analyses will be conducted to determine if motor performance at the end of preschool is predictive of the number of MSK diagnoses throughout the school years after adjusting for age, sex and other important covariates. The interaction between time and motor performance will be examined.

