### Objectives to be explored in the RCT

- 1. To estimate the effect of a motor skills intervention on aberrant movement patterns and musculoskeletal health.

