### Variables

Predictors

- Motor performance as described under ‘core outcomes for all WP’s’
- Movement patterns will be evaluated by kinematic analyses of Drop Vertical Jump Test and Standing Broad Jump Test.

*Drop Vertical Jump Test*

The Drop Vertical Jump Test (DVJ) is a validated clinical test, in which kinematics around the knee are assessed during an accelerated vertical jump from a 31-cm. high box, landing on both feet and immediately followed by vertical jump as high as possible (11). Aberrant movements, including increased valgus motion, high abduction loads, and increased internal rotation of the hip, has repeatedly been shown as a risk factor for (a) anterior cruciate ligament rupture among female athletes (11), and (b) development of patella femoral pain syndrome among female athletes (23, 24) and military recruits of both sexes (25).

*Standing Broad Jump Test (a.k.a. Horizontal Long Jump Test)*

The Standing Broad Jump Test (SBJ) is performed by having the child stand behind a line on the floor, jumping as far as possible, and the length of the jump is measured. It is considered a simple, cheap and safe test, suitable for the assessment of lower body maximal strength in adolescents (26). SBJ has been tested on children as young as 5 years of age, and found to have normally distributed total scores and good reliability (ICC=0.88) (27). Furthermore, it has been used to monitor children with either low or high motor competence with significant discriminative abilities over a 5 years’ period (28).

*Measurement equipment*

The DVJ and SBJ tests will be measured using the Captury motion capture system ([www.thecaptury.com](http://www.thecaptury.com)). The Captury is a portable 8-camera high-speed motion capture system which makes no use of any markers, suits or special hardware. A child avatar has been specially developed to be used in the present project in collaboration with Institute of Sports Science and Clinical Biomechanics, University of Southern Denmark. The Captury has been found to be reliable compared to the Vicon motion capture system used as gold standard (unpublished data, article under preparation).

Outcome

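### WP 3 analyses its randomised movement objective only as a yes/no outcome, which for a roughly normal score gives up at least 36% of the information in the motion-capture data

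*Protocol*

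**What the plan says.** WP 3 has one objective for the randomised comparison: "To estimate the effect of a motor skills intervention on aberrant movement patterns and musculoskeletal health".

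On measurement, WP 3, Variables, states: "Movement patterns will be evaluated by kinematic analyses of Drop Vertical Jump Test and Standing Broad Jump Test". Both tests are recorded with an eight-camera motion capture system.

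On what counts as aberrant, the drop-jump text gives directions without values: "Aberrant movements, including increased valgus motion, high abduction loads, and increased internal rotation of the hip". The reason for interest is that such movement "has repeatedly been shown as a risk factor for (a) anterior cruciate ligament rupture among female athletes (11" and for "development of patella femoral pain syndrome among female athletes (23, 24) and military recruits of both sexes (25". For the broad jump it reports that "SBJ has been tested on children as young as 5 years of age, and found to have normally distributed total scores and good reliability".

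On analysis, WP 3, Analyses, states: "Multilevel logistic regression will be conducted to determine if there was a difference in aberrant movement problems by intervention group". The adjustment terms are time in the intervention, covariates found imbalanced in WP 1, school and the school's socioeconomic status. A baseline value of the outcome is not among them. No continuous analysis of the movement data is named for the randomised comparison.

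Movement patterns stand under Predictors in WP 3, Variables. The three outcomes listed at the end of that section are parent-reported pain, how problems were detected, and diagnoses of persistent problems.

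**The concern.** The measurement is fine-grained and the analysis is coarse. A logistic model uses only the side of a boundary on which a child falls. A shift of the whole distribution then shows only through the children who cross that boundary. The binary reading of the model is secure: where the protocol wants ordered categories (parents' perception in WP 1) it says ordinal regression.

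The choice also departs from the protocol's own practice. WP 1 (motor skills), WP 4, WP 6 and WP 7 analyse scored outcomes with multilevel or mixed linear models adjusted for the baseline value.

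A second, separate question is whether any boundary can be defended at this age. The injury-risk evidence cited for drop-jump movement is from athletes and recruits, while the trial children start at age three. A continuous analysis needs no boundary. At stake is the chance of detecting a real change in movement with data that will be collected anyway.

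**Working it through.** WP 3 states no sample size, power, effect size, standard deviation, intracluster correlation, cut-off or prevalence of aberrant movement, so there is no figure to reproduce. The assumptions below are not from the protocol: a normal score with equal standard deviations, the same shift in every child, 1:1 allocation, clustering ignored, and a range for p, the share of control children classed aberrant.

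**Step 1: information kept by a yes/no split.** For a small shift, relative to comparing means, it is φ(z)² / [p(1−p)], where z is the normal quantile that leaves p in the tail and φ is the normal density.

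| p | z | φ(z) | p(1−p) | kept | lost |
|---|---|---|---|---|---|
| 50% | 0 | 0.39894 | 0.25 | 0.637 | 36% |
| 30% | 0.5244 | 0.3477 | 0.21 | 0.576 | 42% |
| 20% | 0.8416 | 0.2800 | 0.16 | 0.490 | 51% |
| 10% | 1.2816 | 0.1755 | 0.09 | 0.342 | 66% |
| 5% | 1.6449 | 0.1031 | 0.0475 | 0.224 | 78% |

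The median split is the best case, so 36% is the minimum loss. Solving for 0.5 kept gives p = 0.209, so more than half is lost only when fewer than about 21% are classed aberrant.

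**Step 2: the same at a finite effect.** Take a shift of d = 0.3 SD, two-sided alpha 0.05 and power 0.80.

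Continuous, per arm: 2(1.960 + 0.8416)² / 0.3² = 174.4, so 175.

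Binary: the intervention-arm share is p₂ = 1 − Φ(z + d). Per arm, n = [1.960√(2p̄(1−p̄)) + 0.8416√(p(1−p) + p₂(1−p₂))]² / (p − p₂)², where p̄ is the mean of p and p₂.

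| p | p₂ | n per arm | ratio to 175 | power with 175 |
|---|---|---|---|---|
| 50% | 38.2% | 278 | 1.59 | 60% |
| 30% | 20.5% | 327 | 1.87 | 54% |
| 20% | 12.7% | 400 | 2.29 | 46% |
| 10% | 5.7% | 609 | 3.48 | 32% |
| 5% | 2.6% | 986 | 5.63 | 22% |

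For p from 50% to 5%, the ratio runs from 1.58 to 5.18 at d = 0.2 and from 1.62 to 6.86 at d = 0.5. At d = 0.5 a 30% cut already loses half, so the 21% figure belongs to small shifts.

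**Step 3: limits.** Clustering by preschool reduces the effective sample size of both versions. With no intracluster correlation given, the ratios are approximate and the numbers per arm are not planning figures.

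**The case against.** The strongest reply is that the objective asks about aberrant patterns. Whether fewer children move aberrantly is a legitimate question, and a mean difference in degrees could lie wholly within the normal range. That stands, and is why the binary result should be kept.

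The calculation also assumes a uniform shift. The WP 6 background expects stronger effects in children who start with poor motor skills, and WP 1 repeats its analyses in such children. If kinematic benefit is likewise concentrated in the tail, a tail outcome loses less than the tables show. That stands too.

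Several stronger readings are tempting but not supported:
- **That the cut-off is imported from athletes or recruits.** The protocol cites those groups to explain its interest in valgus, abduction load and hip rotation. It gives no cut-off and no source for one. The cut-off may be set in an analysis plan not shown here, so its absence is not the finding.
- **That most of the signal is lost.** This depends on a prevalence the protocol does not give.
- **That growth across a cut-off distorts the comparison.** The arms are randomised and mature concurrently, and WP 3 lists age as a covariate.
- **That jump length is dichotomised.** The term aberrant is tied to the drop jump only, and the broad jump is presented as a strength test.

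Finally, this is an exploratory objective. The WP 1 primary outcome, MovementABC-2 at 18 months, is untouched.

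**Conclusion.** The concern holds in a limited form. The protocol fixes a yes/no analysis as the only randomised comparison of movement patterns, although the source data are kinematic. Under a roughly normal score and a uniform shift, the loss is at least 36%, and exceeds half when fewer than about 21% of children are classed aberrant. In sample-size terms at d = 0.3, the binary analysis needs 1.6 times as many children at a median cut and 5.6 times as many at 5%. The size depends on the unstated prevalence and on how benefit is distributed.

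On validity, the supportable statement is only that no cited evidence backs a particular boundary in preschool children.

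There is also an internal inconsistency: the WP 3 objective and analysis treat movement patterns as a trial outcome, whereas WP 3, Variables, files them under Predictors and omits them from its three outcomes. Overall this is an inexpensive improvement to a secondary part of the programme and does not threaten the trial's main result.

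**What to change.** In WP 3, Analyses, make the main randomised movement comparison a multilevel linear model of one named continuous drop-jump measure (for example peak knee valgus). Adjust it for age and for its baseline value where measured, alongside the terms already listed. Treat other kinematic measures as supportive, so that replacing one outcome does not create several competing ones. Keep the logistic analysis of aberrant movement as a supportive result, because it answers the objective as worded.

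In the same edit, list movement patterns among the RCT outcomes in WP 3, Variables, so that objective, variables and analysis agree.

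The change is to wording only and needs no new measurement. The costs are that the main effect is reported in degrees and not as a risk, and that the investigators must choose the lead measure in advance.

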## Analyses of effect

Simple univariate statistics will be used to describe the outcomes and covariates by preschool. Bivariate analysis adjusted for the design effect will be done to determine if there were any imbalances in the baseline covariates among the two groups.

Multilevel linear regression models will be constructed to assess the effectiveness of the intervention on motor skill performance. The baseline value of the outcome variable, time since baseline, intervention group and any imbalanced covariates will be added to the model along with preschool and socioeconomic status of the area as random effects. The interaction between preschool and intervention group will be tested. The assumptions for the models will be checked.

Multilevel ordinal regression models will be constructed to assess the effectiveness of the intervention on the parents’ perception of their child’s motor competence. The baseline value of the parents’ perception, time since baseline, intervention group and imbalanced covariates will be independent variables. The school and socioeconomic status of the area will be entered as random effects and the interaction between school and intervention will be tested. The model’s assumptions will be tested.

The above analyses will be repeated on a subsample of children who were considered to have a ‘poor’ level of motor competence at baseline.

An analysis will be conducted to determine if the children who dropped out of the study were different from those who remained, based on the baseline values of the outcome variables and the covariates.

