81. Compared to previously used methods using this method will likely improve compliance rates, improve the control of non-wear time and the quality of measurement since the accelerometer keeps the same position on the body and follows the movement of the body. This method has previously been applied in 900 Danish children 9-14 years of age (8).
82. The instrument will be attached to the body using skin-friendly and permeable adhesive patches. If the children participating in this project have eczema or other skin problems, they will be offered to wear an instrument in a belt.
83. We have previously used accelerometers to assess physical activity among large groups of children in this age-group (9-11). The monitors will be initialized to record data during six consecutive days in raw sampling format, which makes it suitable for detecting the short bursts of activity that are typical of preschool children. Sports participation will be obtained from school age using parental-reported SMS as described in WP 3 and previously obtained in the CHAMPS-DK study (12).
84. *Analysis plan*
85. Mixed model linear regression will be used to compare 3-year changes in physical activity and adiposity
86. between children in the intervention group and control group with appropriate adjustment for imbalanced
87. covariates and baseline levels of the outcomes. Bi-directional association between motor skills
88. development and change in physical activity and sports participation will be analyzed in a cohort approach
89. using mixed model regression with adjustment for experimental allocation group and other putative
90. determinants of motor skills and physical activity.
91. Annually obtained information on motor skills will be used to calculate percentile curves for motor skills
92. from age 3 to 5 years to illustrate the developmental course and provide age- and sex-specific variability in
93. a community-wide sample of apparently healthy children.
94. **Primary responsibility**
95. Associate [name] (Head of Research Unit for Exercise Epidemiology and Research in
96. Childhood Health), Department of Sports Science and Clinical Biomechanics, University of Southern
97. Denmark.
98. **References**
99. 1. Burgi F, Meyer U, Granacher U, Schindler C, Marques-Vidal P, Kriemler S, et al. Relationship of physical
100. activity with motor skills, aerobic fitness and body fat in preschool children: a cross-sectional and

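### WP 3's between-arm model of aberrant movement does not name the child's baseline movement result; if jump tests precede the intervention, it gives up power and leaves a chance baseline imbalance uncorrected

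*Protocol*

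**What the plan says.** WP 3 has one randomised objective: "To estimate the effect of a motor skills intervention on aberrant movement patterns and musculoskeletal health". On measurement, WP 3, Variables says: "Movement patterns will be evaluated by kinematic analyses of Drop Vertical Jump Test and Standing Broad Jump Test". It gives no test times.

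The between-arm model in WP 3, Analyses is a multilevel logistic regression with this target and adjustment: "difference in aberrant movement problems by intervention group after adjusting for time in intervention, imbalanced covariates from WP1, school and socioeconomic status of the school". WP 3, Covariates adds "sex, age, socioeconomic status, child well-being and parental MSK health". Neither place names the child's movement result at baseline.

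The other work packages do name the baseline outcome:

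- WP 1, Analyses of effect (motor skills), and WP 6, Analyses (wellbeing), use the same sentence: "The baseline value of the outcome variable, time since baseline, intervention group and any imbalanced covariates will be added to the model". WP 1 also puts the baseline rating into its ordinal model of parents' perception.
- WP 4, Analysis plan adjusts for imbalanced "covariates and baseline levels of the outcomes".
- WP 7, Analyses lists the baseline outcome first in its executive-function model.

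For the cohort, WP 3 states: "Multilevel longitudinal logistic regression analyses will be conducted to determine if poor motor performance is associated with aberrant movement patterns", followed by: "The interaction between time and poor motor performance will be examined".

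**The concern.** The baseline value of an outcome is usually among its strongest predictors, and four sibling work packages use it. The WP 3 movement model gives no reason for leaving it out.

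The model's provision for imbalance does not clearly help. It brings in covariates found imbalanced in WP 1, but jump kinematics are defined only in WP 3. A baseline difference in aberrant movement could therefore be seen and still have no stated way into the model.

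Two things are at stake in the movement part of WP 3's only randomised objective: power, and the ability to correct a difference between arms that was present at the start. The second matters more if whole preschools are allocated, because there are then fewer independent units to even out. WP 1 points that way, with its design effect, preschool random effect and mention of experience with cluster trials, but this document does not state the allocation unit outright.

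**Working it through.** **No stated figure to reproduce.** The document gives no sample size, power, prevalence, correlation or number of preschools for this analysis. Every number below rests on assumed inputs.

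**Step 1: compare the stated between-arm models.**

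| Model | Baseline outcome included? |
| --- | --- |
| WP 1 motor skills; WP 1 parents' perception | Yes; yes |
| WP 4 physical activity and adiposity | Yes |
| WP 6 wellbeing | Yes |
| WP 7 executive function | Yes |
| WP 3 aberrant movement (logistic) | No |
| WP 3 diagnoses (Poisson) | No, but the outcome is a count accruing over follow-up |
| WP 5 language | No between-arm model stated |

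**Step 2: is a baseline value available?** The longitudinal logistic model with a time interaction implies that movement is measured more than once. It does not show that the first measurement precedes the intervention. The rest of the working assumes that it does.

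**Step 3: power.** Assumed inputs: 200 children per arm, no clustering, binary baseline, conditional treatment log odds ratio -0.5, and 1,500 simulated trials per setting. Power without and with the baseline term:

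| Baseline-to-follow-up log OR | Prevalence 20% | Prevalence 40% |
| --- | --- | --- |
| 1 | 44% to 44% | 61% to 63% |
| 2 | 38% to 44% | 48% to 57% |
| 3 | 28% to 38% | 29% to 44% |

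The gain runs from about nil to 15 points. The standard deviation of the estimated risk difference falls by 1% (0.0376 to 0.0372; log OR 1, prevalence 20%) to 23% (0.0481 to 0.0372; log OR 3, prevalence 40%).

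The standard error of the log odds ratio does not fall. At log OR 2 and prevalence 40% it rises from 0.209 to 0.237, while the mean estimate moves from -0.399 to -0.502. The ratio of estimate to standard error grows from 0.399/0.209 = 1.91 to 0.502/0.237 = 2.12, and that is the source of the power.

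**Step 4: how likely is a chance imbalance?** Assume prevalence p = 0.30, m = 20 children per preschool, ICC 0.05 and k preschools per arm. Then SE = sqrt(2p(1-p)(1+(m-1)ICC)/(km)), and the numerator is 0.42 x 1.95 = 0.819.

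- k = 8: sqrt(0.819/160) = 7.2 points, so P(difference above 5 points in either direction) = 48%.
- k = 20: sqrt(0.819/400) = 4.5 points, so the same probability is 27%.

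**Step 5: what does an imbalance do if there is no true effect?** Assume a bivariate-normal latent scale with baseline-to-follow-up correlation 0.5.

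- 35% v 30% at baseline: the latent shift is -0.385 - (-0.524) = 0.139, and half of it is 0.070. Expected follow-up prevalence is 32.5% v 30%, an odds ratio of 1.12.
- 40% v 30%: the latent shift is 0.271, and half is 0.136. Expected follow-up prevalence is 34.9% v 30%, an odds ratio of 1.25.

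The simulation agrees in direction. With a 10-point imbalance (35% v 25%), no true effect and baseline log OR 1, 2 and 3, the unadjusted model gives mean log odds ratios of 0.10, 0.19 and 0.29 and rejects in 7%, 14% and 29% of runs. With the baseline term the mean is about 0 and rejection is 4-5%.

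**The case against.** **The baseline test may not exist.** The document never says that jump tests precede the intervention. The longitudinal model serves a cohort objective with 12 years of follow-up, so all its measurements could come later. WP 3 also reports the broad jump as tested in children from 5 years, while the cohort starts at three. This stands. A reader might infer that the plan collects a baseline and then discards it; the document does not support that, and the point is conditional.

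**Randomisation already protects the comparison.** This also stands. A reader might infer that the WP 3 result would be biased as planned. It would not be: the comparison is valid on average over randomisations, and chance imbalance is part of the multilevel model's stated uncertainty. Dividing the Step 4 standard errors by p(1-p) = 0.21 gives 0.34 (k = 8) and 0.22 (k = 20) on the log-odds scale. An odds ratio of 1.12 (log 0.11) is then about one third to one half of a standard error. The rejection rates in Step 5 are conditional on an imbalance having occurred.

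**The standard error is not inflated.** A reader might infer that leaving out baseline enlarges the standard error of the treatment coefficient. In the planned logistic model the reverse holds for the log odds ratio, as Step 3 shows.

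**The covariate lists may not be closed.** WP 3, Covariates supplements the list in WP 3, Analyses, nothing says other covariates are barred, and WP 1 prints no full covariate list here. So it cannot be said that a movement imbalance is formally excluded, only that no route is stated.

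**The sibling wording may be template text.** WP 7 applies it even to Grade 9 examination grades, which can have no preschool baseline. That weakens the comparison for that one model but not for WP 1, WP 4, WP 6 or WP 7's executive-function model.

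**Covariate detail can wait for the SAP.** Often so, but here the protocol states an adjustment set for this model and the baseline outcome is not in it.

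**Conclusion.** The point holds in conditional form. The stated WP 3 adjustment set omits the baseline movement result, unlike the comparable models in four sibling work packages. If a pre-intervention jump test exists, the model gives up power and leaves a realised baseline imbalance in this outcome uncorrected.

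The power cost is about nil to 15 points. Which end applies depends on the unstated baseline-to-follow-up association, and the simulation behind the range ignores clustering. The 27-48% chance of a baseline difference above 5 points depends on the assumed prevalence, ICC, preschool size and number of preschools.

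The change is worth making because it is cheap. It concerns one outcome of one work package; the trial's primary outcome, the MovementABC-2 in WP 1, is unaffected. If no baseline jump test is done, the remedy is unavailable and the point lapses.

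**What to change.** In WP 3, Analyses, add one sentence to the between-arm model of aberrant movement: where a pre-intervention jump test exists, the child's baseline movement result from the drop vertical jump or standing broad jump is always included, whether or not the arms differ on it. Prefer the continuous kinematic value to a yes/no version.

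State that children without a baseline test stay in the model, for example through mean imputation of the baseline covariate with a missing indicator, or multiple imputation. State also when the jump tests take place, or refer to the schedule in the main protocol.

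Because the model is logistic, reporting a standardised risk difference beside the odds ratio would make the gain in precision visible.

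The cost is a sentence or two and no new measurement if the tests are already done at baseline. The small downside is handling missing baseline tests, which could be more common among the youngest children.

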### Objectives to be explored in the full cohort

1. To describe the age and sex related incidence and course of back-, neck- and extremity-disorders in a general paediatric population from three to fifteen years of age.
2. To establish potential patterns of development of musculoskeletal disorders from three to fifteen years of age.
3. To determine the potential relationship between poor motor performance and aberrant movement patterns.
4. To determine the potential relationship between motor performance at the end of preschool and musculoskeletal health throughout the school years.

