***SMS 1 (every second Sunday):***

Do you think you child have had pain from muscles or joints in the past two weeks?

Answer 1 for yes and 2 for no.

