**Perspectives**

The RCT has the potential to show the effect of a motor performance programme on specific movement patterns. Of equal importance, the project will bring new insights into the early phases of MSK problems, including how and why these problems arise and develop and the type of problems children from three to 15 years of age experience. Through this rich dataset, we will be able to identify and recognise risk patterns which are important for preventing future chronic MSK conditions. Together, this opens ‘a window of opportunity’ for implementing targeted prophylactic strategies with the potential to reduce the risk of current and future MSK injuries and their associated individual and societal burden.

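### WP 3 tests the number of musculoskeletal classes against a null with no child-to-child variation within a class, so rejection alone would not show that separate developmental patterns exist

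*Protocol*

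**What the plan says.** The second cohort objective of WP 3 is: "To establish potential patterns of development of musculoskeletal disorders from three to fifteen years of age". The Analyses section of WP 3 names the models: "Longitudinal latent class analysis and latent class growth analysis will be conducted to describe the MSK developmental patterns". It then says how the number of classes will be judged: "The sequential model comparisons (T classes vs. T + 1 classes) and chi-square goodness-of-fit test will be evaluated using the parametric bootstrapping technique". The classes are carried forward: "Lastly, the associations between class membership and the prevalence of related measures will be examined using a confirmatory latent class analysis approach". The Perspectives section states the intended use: "Through this rich dataset, we will be able to identify and recognise risk patterns which are important for preventing future chronic MSK conditions", and goes on to link this to targeted preventive strategies.

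On the data, parents are asked by text message every second Sunday: "Do you think you child have had pain from muscles or joints in the past two weeks". On duration, WP 3 says: "The duration of the follow-up will be 12 years, which covers three years in preschool and nine years in school".

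The WP 3 text does not mention a one-population model with continuous differences between children as an alternative to the class solutions. For its other longitudinal cohort questions the same section uses multilevel longitudinal regression.

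**The concern.** The scientific question is whether children follow several different developmental courses. The test answers a narrower one. As these two models are ordinarily defined, all children in a class have the same response probabilities over time, and a child's reports are independent once class is known. The protocol does not write this out; it follows from the methods it names. A parametric bootstrap simulates from the fitted T-class model, so its null combines two statements: there are T classes, and children within a class do not differ.

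A population in which some children are simply a little more prone to pain than others breaks the second statement without breaking the first. The T versus T+1 test would then reject, and the extra class would be a slice of one distribution. If classes obtained this way are related to other measures and read as risk patterns, the conclusion would go further than the test allows. WP 3 itself gives reason to expect children to differ in level: its covariates include socioeconomic status, child well-being and parental MSK health.

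**Working it through.** The protocol gives no figure for this analysis, so there is none to reproduce. The stated rule was simulated instead.

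**Models.** For child i, wave j and class k, with binary report y:

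- Class model: P(y_i) = Σ_k π_k Π_j p_kj^y_ij (1 − p_kj)^(1 − y_ij). In latent class growth analysis (LCGA), logit p_kj is a polynomial in time with class-specific coefficients. In longitudinal latent class analysis (LLCA), p_kj is free.
- One population, no classes: logit p_ij = trend(t_j) + u_i, with u_i ~ N(0, SD²) and the same trend for every child.

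The one-population likelihood is an integral over u. A small number of support points approximates that integral well, and a few support points are the same thing as a few parallel classes. One would therefore expect the rule to settle on a few classes rather than one.

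**Assumed inputs (none is in the protocol).** Main simulation: 8 binary waves, N = 500 or 1000, mean logit −1.5, 60 datasets per scenario, alpha 0.05, stopping at the first non-rejection, at most 5 classes, and 39 bootstrap samples with p = (1 + number of bootstrap statistics ≥ observed)/40. For scale, a child one SD above average has odds of pain multiplied by e^0.5 = 1.6, e^1 = 2.7, e^1.5 = 4.5 or e^2 = 7.4.

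**Calibration.**

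- With no heterogeneity, the rule kept one class in 58/60 (LCGA) and 59/60 (LLCA).
- With two real classes, it chose two in 55/60 for each model.

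**One population, continuous differences only: number of classes chosen**

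| SD, N | LCGA | LLCA |
| --- | --- | --- |
| 0.5, 500 | one class rejected in 54/60 | not run |
| 1.0, 500 | two 27, three 31, four 2 | two 52, three 8 |
| 1.5, 500 | two 1, three 51, four 7, five 1 | two 5, three 53, four 2 |
| 1.5, 1000 | three 47, four 12, five 1 | three 49, four 10, five 1 |

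At SD 1.0, two or more classes were returned in 60/60 for both models. At SD 1.5 and N 500, three or more were returned in 51 + 7 + 1 = 59/60 and 53 + 2 = 55/60.

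**Bootstrapped chi-square test.** It accepted one class in 55/60 (LCGA) and 56/60 (LLCA) when the population was homogeneous. At SD 1.0 or more it never accepted one class. It first accepted two or three classes in 56 to 58 of 60 datasets (for example 54 + 3 = 57 for LCGA at SD 1.0). It therefore gives no protection.

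**A second, separately written simulation** used LCGA with 12 waves, N = 500, logit p = −2 + 0.2t + u, 19 bootstrap draws and 21 to 25 datasets per SD. At SD 1.0, 1.5 and 2.0 the rejection rates were:

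- 1 vs 2 classes: 100%, 100%, 100%
- 2 vs 3 classes: 80%, 100%, 100%
- 3 vs 4 classes: 4%, 43%, 77%

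When the assumptions held, test size was 7% (1 vs 2, one homogeneous class) and 3% (2 vs 3, two real classes).

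**Does a competitor model separate the cases?** BIC = −2 log L + k log N. The one-population random-intercept model with a quadratic trend has k = 4. LCGA with K classes has k = 3K + (K − 1) = 4K − 1, so 7 for two classes and 11 for three. At N = 500, log N = 6.21 and the penalties are 24.9, 43.5 and 68.4. The one-population model had lower BIC than the best of the 1- to 4-class LCGA fits in:

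- 55/60 (SD 0.5, N 500), 60/60 (SD 1.0, N 500), 60/60 (SD 1.5, N 500) and 60/60 (SD 1.5, N 1000) when differences were continuous;
- 4/60 when two real classes generated the data.

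**The case against.** The strongest reply is that latent class growth models are a recognised way to summarise a continuum by a few typical courses, with no claim that subpopulations exist. WP 3 speaks of describing patterns, its objective says potential patterns, and Perspectives credits the dataset as a whole, not class membership, with revealing risk patterns. That stands as far as it goes. It is a reason to word the conclusion conditionally, but it does not make the test informative about whether separate patterns exist.

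The rule is also partly inferred. The text gives no significance level or stopping rule and does not say that rejection alone fixes the number of classes. Further criteria may be in a statistical analysis plan that is not shown, so their absence is not held against the protocol. Nor does WP 3 say which of its three outcomes enters the latent class models: the two-weekly questions belong to the preschool years, while the objective runs to age fifteen.

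A reader might infer four stronger things, none of which is supported:

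- **WP 3 will report false patterns.** That depends on how children really differ, which is unknown.
- **The sequence keeps adding classes, more so with more reports.** At SD 1.0 it levels off at two or three (3 vs 4 rejected in 4%). Sample size was varied only at SD 1.5, and the number of reports was not varied within either simulation.
- **Serial dependence is a demonstrated second cause.** It is plausible, but only a random intercept was simulated.
- **The trial's effect estimates are at risk.** This is a cohort objective, listed separately from the randomised one.

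Finally, the competitor was tested on data with a normal random intercept, which is its most favourable case.

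**Conclusion.** The point holds in conditional form. With the two models named, rejecting T classes shows that T homogeneous classes do not fit; it does not show that a further developmental pattern exists. If children differ in pain level on a continuum, the rule would reject a single class in about 90% of datasets at SD 0.5 (54/60) and in all of them at SD 1.0 or above. It would typically return two or three classes, and four or more in a minority at SD 1.5 and in most datasets at SD 2.0 with 12 waves. The chi-square test pushes the same way.

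These sizes rest on assumed waves, sample sizes, SDs, alpha and stopping rule. The direction was the same throughout the range tried, and the rule was well calibrated when its assumptions held. The consequence is limited to what WP 3 may conclude about MSK patterns and their correlates. The change is a cheap improvement to one descriptive cohort analysis; the randomised comparisons and the primary outcome are not touched.

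**What to change.** Add to the Analyses section of WP 3:

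1. Fit a one-class random-effects longitudinal model (child-level random intercept, and random slope where estimable) to the same data as the latent class models, and compare it by BIC with the 1- to T-class solutions.
2. Interpret classes as separate developmental patterns only if they beat that model. Otherwise present them as descriptive summaries of a continuum, and relate the continuous child-level effect, not class membership, to the other measures.
3. Word the Perspectives section to match.

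Growth-mixture models, which allow variation within classes, may be added as a sensitivity analysis. They were not tested here, and they replace one within-class assumption with another. Reappearance of the classes in a random half of the sample should not be the criterion, because slices of a continuum would also tend to reappear.

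The cost is a few more models on data already being collected, and possibly fewer patterns claimed.
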